#### 14.4.6 INFLUENCE FACTORS (MOTHER)

- Antenatal administration of steroids (yes or no).
- Presence of premature rupture of membranes (in hours)
- Presence of preeclampsia and/or HELLP syndrome (yes/no in each case)
- Highest CRP level in the period 48 hours before birth
- Number of previous pregnancies (not including the current pregnancy)
- Presence of CMV-specific IgM and IgG antibodies in the period  $\pm 2$  weeks peripartum (in each case yes or no)
- Experience of the obstetrician performing caesarean section (number of caesarean sections performed for preterm infants < 1500 g birth weight:  $n > 100$  or  $n < 100$ )

#### 14.4.7 TARGET MATERNAL VARIABLES

- Blood loss during labour (in ml).
- Minimal Hb level in 24 hours after delivery (in g/dl)
- Survival until discharge from hospital ("yes" or "no")
- Duration of hospitalization (in days)

### 14.5 EXPERIMENTAL PART

- Serum analysis by multiplex angiogenesis panel, taken from the umbilical cord after cord clamping:
  - **Pro- and anti-inflammatory cytokines:** IL-1 $\alpha$ , IL-1 $\beta$ , IL-6, IL-10, IL-12 (p40), IL-12 (p70), IL-13, IL-17A, granulocyte colony-stimulating factor (G-CSF), granulocyte/macrophage colony-stimulating factor (GM-CSF), monocyte chemotactic protein-1 (MCP-1), macrophage inflammatory protein-1 $\alpha$  (MIP-1 $\alpha$ ), MIP-1 $\beta$ , CXCL10,
  - **Factors of Angiogenesis:** sALK-1, amphiregulin, TGF $\alpha$ , epidermal growth factor (EGF), angiopoietin-1/2, sCD31/PECAM-1, endoglin, endothelin-1, basic fibroblast factor (FGF2), hepatocyte growth factor (HGF), leptin, placental growth factor-2 (PLGF-2), prolactin, vascular endothelial growth factor-A (VEGF-A), VEGF-C and VEGF-D, Placental growth factor (PGF), BMP2, BMP4, BMP7, TGF $\beta$ , apelin
- Serum analysis of 0.5 ml blood sample collected on day 28 of life ( $\pm 2$  days) as part of a medically indicated blood collection. Analysis by multiplex angiogenesis panel on:
  - **Pro- and anti-inflammatory cytokines:** IL-1 $\alpha$ , IL-1 $\beta$ , IL-6, IL-10, IL-12 (p40), IL-12 (p70), IL-13, IL-17A, granulocyte colony-stimulating factor (G-CSF), granulocyte/macrophage colony-stimulating factor (GM-CSF), monocyte chemotactic protein-1 (MCP-1), macrophage inflammatory protein-1 $\alpha$  (MIP-1 $\alpha$ ), MIP-1 $\beta$ , CXCL10,

- **Factors of Angiogenesis:** sALK-1, amphiregulin, TGF $\alpha$ , epidermal growth factor (EGF), angiopoietin-1/2, sCD31/PECAM-1, endoglin, endothelin-1, basic fibroblast factor (FGF2), hepatocyte growth factor (HGF), leptin, placental growth factor-2 (PLGF-2), prolactin, vascular endothelial growth factor-A (VEGF-A), VEGF-C and VEGF-D, Placental growth factor (PGF), BMP2, BMP4, BMP7, TGF $\beta$ , apelin

Differences and changes in the panel variables are described with fold change (to base 2) and evaluated with distribution-free procedures (Wilcoxon rank sum or Wilcoxon signed rank test). The false discovery rate is controlled at 5% (Benjamini Y, Hochberg Y: Controlling the false discovery rate: a practical and powerful approach to multiple testing. Journal of the Royal Statistic Society 1995; 57: 298-300).

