### **9.3 NUMBER OF PARTICIPANTS**

60 births (including approximately 30% twin births) will be included. In the case of twins, for medical reasons, only the second-born infant can be randomized. The first-born infant will receive the control treatment.

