### **9.4 METHODS FOR ASSIGNING PARTICIPANTS TO TREATMENT GROUPS**

Participants will be assigned randomly to study group treatments in a 1:1 ratio according to a blocked sequence of computer-generated, pseudorandom codes. Randomization is provided as a set of opaque numbered letters by the Institute of Medical Statistics and Bioinformatics at the University of Cologne. Randomization will be stratified by:

- Gestational age: 1) 24+0 - 27 + 6 SSW, 2) > 27+6 SSW.
- Type of gravidity: 1) singleton, 2) multiple

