### **14.3 PRIMARY TARGET VARIABLE**

The primary target variable is the mean haematocrit value in the first 24 hours after birth.

The hematocrit value is given as percentage. If there are > 1 measured values per patient, the arithmetic mean is determined. Group comparison is done by covariance analysis (ANCOVA) with fixed effects: baseline, group, gestational age (24+0 - 27 + 6 SSW vs. > 27+6 SSW) and gravidity (singleton vs. multiples). The influence of missing values is considered and explored via multiple substitutions (sensitivity analysis).

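### The serum panel's between-arm rank-sum test ignores the two randomisation factors, so it stays valid but is conservative and forgoes power for markers that vary with gestational age or gravidity

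*Protocol*

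**What the plan says.** The design and the primary analysis both use two factors that the panel analysis leaves out.

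- **Randomisation (9.4).** Allocation is "in a 1:1 ratio according to a blocked sequence of computer-generated, pseudorandom codes". The strata are "Gestational age: 1) 24+0 - 27 + 6 SSW, 2) > 27+6 SSW" and "Type of gravidity: 1) singleton, 2) multiple".
- **Size (9.3).** "60 births (including approximately 30% twin births) will be included". Only the second twin is randomised.
- **Primary analysis (14.3).** The ANCOVA of mean haematocrit has among its fixed effects "gestational age (24+0 - 27 + 6 SSW vs. > 27+6 SSW) and gravidity (singleton vs. multiples"). Section 14.7 relies on such covariates to make up for power lost to missing values.
- **Serum panel (14.5).** Analytes measured in cord blood and on day 28 are "evaluated with distribution-free procedures (Wilcoxon rank sum or Wilcoxon signed rank test"). On multiplicity: "The false discovery rate is controlled at 5" per cent, by the Benjamini-Hochberg method. No stratified version and no covariate is mentioned.

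The rank-sum test serves the comparison of arms. The signed-rank test serves change within an infant and is not at issue.

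**The concern.** Blocking within strata forces the arms to be nearly equal in gestational-age class and gravidity. If a marker differs between those classes, the difference between arms varies less from trial to trial than it would under simple randomisation. The plain rank-sum test does not know this. Its null variance assumes that every split of the 60 infants was possible, so it still counts the spread between strata as noise. The p-values come out too large on average.

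At stake is sensitivity. Many analytes are tested on few infants under false discovery rate control, which calls for p-values well below 0.05, and that is where needless noise costs most.

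**Working it through.** **The plan's own figure.** The protocol states no size or power for the panel. Its only sample size concerns haematocrit (14.7): 52.1 ± 6.6 against 57.31 ± 7.26, unequal-variance t test, two-sided. With alpha taken as 5% (14.7 gives no number), power is 0.788 at 28 per arm and 0.802 at 29, so 2 × 29 is reproduced. It says nothing about the panel.

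**Number of tests.** Section 14.5 lists 14 cytokines and 23 angiogenic factors (angiopoietin-1/2 counted as two). That is 37 analytes × 2 time points = 74 between-arm tests.

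**Inputs.** From the protocol: 60 randomised infants, 1:1, four strata, about 30% twins. Assumed, because the protocol does not say: blocks of 4, half the infants in each gestational-age class, a normal marker on the log scale, and an arm effect of 0.75 SD (about 80% power with no maturity effect).

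**From class gap to variance share.** For two equal classes that differ by d within-stratum SDs, the share explained is R² = (d²/4) / (1 + d²/4). For d = 0.5, 0.0625/1.0625 = 6%. For d = 1, 0.25/1.25 = 20%. For d = 2, 1/2 = 50%.

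**Approximate type I error.** With balanced strata the variance of the unadjusted statistic shrinks to about (1 − R²) of its assumed value. The true error is therefore about 2Φ(−1.96/√(1 − R²)).
- R² = 10%: 1.96/0.949 = 2.07, error 3.9%
- R² = 20%: 1.96/0.894 = 2.19, error 2.8%
- R² = 50%: 1.96/0.707 = 2.77, error 0.6%

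**Simulation with within-stratum SD fixed** (8,000 runs per setting, nominal two-sided 5%):

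| Class gap (SD) | Type I: rank sum / van Elteren / rank ANCOVA | Power: rank sum / van Elteren / rank ANCOVA |
|---|---|---|
| 0 | 5.1 / 5.1 / 5.1% | 79.5 / 77.5 / 79.7% |
| 0.5 | 4.7 / 5.2 / 5.5% | 77.6 / 77.1 / 79.4% |
| 1 | 3.0 / 4.8 / 4.8% | 71.8 / 77.7 / 79.6% |
| 2 | 0.5 / 4.7 / 4.9% | 46.9 / 77.3 / 78.5% |

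Blocks of 6 gave the same rank-sum error at a 1 SD gap (3.1%). With unstratified allocation and the same gap the error was 4.6%, so the conservatism comes mainly from stratifying and then ignoring the strata.

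**Simulation with total SD fixed** (arm effect 0.75 total SD). At R² = 20%, the rank-sum type I error is 3.1% and its power 82%, against 86% for van Elteren and 88% for rank ANCOVA. At R² = 10% the gain is 1–3 points; at 0% there is none.

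**Under false discovery rate control.** The Benjamini-Hochberg cut-off with k discoveries is 0.05 × k/74. A level of 0.005 corresponds to k = 0.005 × 74/0.05 = 7.4, so it illustrates the case where about seven markers are declared. At that level and R² = 20%, power is 45% for the rank sum, 56% for van Elteren and 60% for rank ANCOVA.

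**The case against.** The strongest reply is that nothing here is an error. The rank-sum test with false discovery rate control is standard, its only fault is caution, section 14.1 calls the analysis largely descriptive, and 14.3 ties the strata to the primary model alone. Whether an exploratory test is stratified could be settled in an analysis plan that is not shown. Most of this stands and sets the ceiling on severity. But 14.5 does fix the test by name, and reading it as unstratified is the natural sense beside a primary analysis that lists both factors.

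The benefit is also assumed. A 20% share means a full 1 SD gap between the gestational-age classes, and one share cannot fit 37 mixed analytes. Nor does every adjusted test help everywhere: van Elteren costs 2–4 points when a marker is unrelated to the strata. The day-28 sample depends on a medically indicated draw, so fewer infants are likely. With an assumed 25% missing, van Elteren costs 3–4 points at a 0% share, gains under 1 point at 10%, and still gains 5–6 at 20%. All of this stands, and it favours rank ANCOVA.

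Three stronger inferences are not supported:
- **That the rank-sum test is the only other comparison of EPT with DCC that the plan specifies.** Section 14.7 also sets a paired t-test of the EPT twins against their siblings, and 14.6 plans subgroup analyses by the same two factors. Neither adjusts the panel tests.
- **That missed differences decide whether the endothelial-cell step is run.** Section 10.2.2.3 makes that step depend on abnormalities without defining them as significant arm differences, and also on the residual serum.
- **That the plain test's power necessarily falls.** It falls if within-stratum SD is held fixed (79.5% to 71.8% at a 1 SD gap). If total SD is held fixed it rises slightly, and the loss is a gain forgone.

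**Conclusion.** The point holds as a minor improvement. The planned between-arm panel test is valid, does not inflate false positives, and contradicts no other section. It does leave unused the two factors on which the trial stratifies. For a marker with a 20% share explained by gestational-age class, the price is a true error near 3% instead of 5%, 4–6 points of power at nominal 5%, and 11–15 points at a per-test level of 0.005. For weakly related markers the price is small, and for unrelated markers it is nil. The size rests on the assumed variance share, an arm effect of 0.75 SD, an even gestational-age split and near-complete samples. The direction rests only on the stratified blocking and on the marker varying with the strata.

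**What to change.** In 14.5, state that between-arm comparisons of panel variables use a rank-based test adjusted for the randomisation factors. The preferred form is rank ANCOVA on gestational-age class (24+0–27+6 against >27+6) and gravidity (singleton against multiple). It shows no material loss when a marker is unrelated to the strata (79.7% against 79.5% in the simulation). The van Elteren test stratified by the same factors is an acceptable alternative. Its price is about 2–4 points of power for unrelated markers, because the multiple-birth strata are small. Keep Benjamini-Hochberg at 5%, and leave the within-infant signed-rank test as it is.

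The cost is one sentence. The factors are already recorded for every randomised infant, and no further samples or infants are needed.

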#### 14.6 SUBGROUP ANALYSIS

Subgroup analyses will be performed by gestational age (group 1 23+6 - 27+6 SSW, group 2 > 28+0 SSW), sex, and mode of pregnancy (singleton vs. multiples).

#### 14.7 SAMPLE CALCULATION

Our hypothesis is that EPT increases the averaged hematocrit value in the first 24 hours after birth by (relative) 10% (primary outcome), ie, according to (10) from 52.1 $\pm$ 6.6% (Table II, DCC only) to 57.31 $\pm$ 7.26%. To detect this difference with the two-sample t test for unequal variances in two-sided error of 1st kind with a power of 80%, a case number of 2 times 29 evaluable patients, i.e. about 60 patients, is required (Stata 15.1, StataCorp LLC, College Station, TX, USA; power twomeans). By accounting for covariates (baseline, gestational age, gravity) in ANCOVA, the power reduction due to any missing values can be compensated for. Furthermore, the nine twins randomized to EPT will be compared to their control siblings, where the paired t-test still achieves a power of 80% with a one-sided error of 1st kind of 10% and a correlation of 0.5 between the two measurements (power pairedmeans).

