### **7.3 FEASIBILITY**

Another aim of the study is to investigate the feasibility of EPT.

According to conservative estimates, in 10-20% of elective cesarean deliveries it is not possible to deliver the placenta together with the infant. Possible reasons for this are, for example, a deep position of the placenta, adhesions and a possible maternal blood loss. In addition, the feasibility of EPT after birth of the infant in the context of neonatal resuscitation will be investigated.

Therefore, another aim of the study is to evaluate the frequency with which EPT is not feasible and to detect possible influencing factors.

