## **9.6 PROCEDURE IN CASE OF NON-FEASIBILITY OF THE INTERVENTION**

If it is not possible to perform study intervention for medical reasons (despite assignment to the intervention group), the participant remains in the study (intention-to-treat principle).

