#### 10.2.1.6 PROCEDURE IF INTERVENTION IS NOT PERFORMED

If, despite allocation of the infant to the intervention group, the development of the placenta by obstetrics is not possible (e.g. deep placental position) or if there are concerns by the obstetrics (long duration of development, maternal complications such as severe blood loss, etc.), it is up to obstetrics to stop the intervention in this situation and, if necessary, to immediately clamp the cord (ICC) or perform umbilical cord milking (CM). In this case, the further procedure of neonatal resuscitation is

based on the procedure of the control group. Nevertheless, the collection of primary and secondary target criteria is performed. (intention-to-treat principle).

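### The 80% power in 14.7 makes no allowance for the 10–20% EPT non-feasibility that 7.3 expects and that the ITT analysis keeps in the EPT arm

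*Protocol*

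**What the plan says.** **Sizing (Protocol 14.7).** The hypothesis is that "EPT increases the averaged hematocrit value in the first 24 hours after birth by (relative) 10% (primary outcome", from 52.1 (SD 6.6) under DCC to 57.31 (SD 7.26). The test is a two-sample t test for unequal variances, "in two-sided error of 1st kind with a power of 80"%. The conclusion is that "a case number of 2 times 29 evaluable patients, i.e. about 60 patients, is required". The only buffer mentioned is the gain from ANCOVA covariates, which the section sets against missing values. Non-feasibility of EPT is not mentioned.

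**Expected non-feasibility (Protocol 7.3).** By what the section calls conservative estimates, "in 10-20% of elective cesarean deliveries it is not possible to deliver the placenta together with the infant". Feasibility during resuscitation is to be studied as well, with no rate given.

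**Handling.** Section 9.6 says that if EPT cannot be performed for medical reasons, "the participant remains in the study (intention-to-treat principle"). Section 10.2.1.6 says "it is up to obstetrics to stop the intervention in this situation and, if necessary, to immediately clamp the cord (ICC") or to milk the cord; care then follows the control-group procedure and outcomes are still collected. Section 14.2 makes ITT, by assigned arm, the primary analysis set and treats intercurrent events as irrelevant to it.

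**The concern.** Three statements meet here: an expected failure rate of 10–20% in one arm, a primary analysis that counts those failures in that arm, and a power calculation that gives the whole arm the full effect. If the 10% rise belongs to EPT as performed, the expected ITT difference is smaller than 5.21 points and 29 per arm no longer gives 80% power.

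What is at stake is how the result is read. The planned 20% risk of missing a real 5.21-point effect could be nearer 30–40%. A non-significant result would then be weaker evidence against an effect of EPT than the protocol's power statement implies. The planned 30 per arm leaves one infant per arm above the 29 required, so recruitment adds almost no reserve.

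**Working it through.** **Inputs**

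- Means 52.1 and 57.31, difference d = 5.21; SDs 6.6 (DCC) and 7.26 (EPT): section 14.7.
- Two-sided alpha of 5%: 14.7 gives no number. It is inferred from the 95% confidence level in 14.1 and supported by the reproduction below.
- n = 29 evaluable per arm (14.7); 30 per arm planned (Synopsis).
- Non-feasible share f = 0.10 to 0.20 (7.3), carried over from elective caesareans to this trial.
- Mean and SD in non-feasible infants: not in the documents. Assumed SD 6.6 and mean 52.1 + k, with k = 0 as the reference case and k = −2.6 and +2.6 (about half of 5.21) as an illustrative range.

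**Step 1: reproduce the stated figure.** Welch t test with the noncentral t distribution. SE = √(6.6²/n + 7.26²/n); noncentrality = 5.21/SE.

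- n = 28: SE 1.854, noncentrality 2.810, power 78.8%.
- n = 29: SE 1.822, noncentrality 2.860, power 80.2%.

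The smallest n reaching 80% is 29, as stated.

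**Step 2: dilute the EPT arm.**

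- ITT difference = (1 − f) × 5.21 + f × k
- EPT-arm variance = (1 − f) × 7.26² + f × 6.6² + f(1 − f) × (5.21 − k)²

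For k = 0:

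- f = 0.10: difference 0.9 × 5.21 = 4.69; variance 47.44 + 4.36 + 2.44 = 54.24, SD 7.36. At n = 29, SE 1.836 and noncentrality 2.553.
- f = 0.20: difference 0.8 × 5.21 = 4.17; variance 42.17 + 8.71 + 4.34 = 55.22, SD 7.43. At n = 29, SE 1.846 and noncentrality 2.258.

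| Non-feasible infants' mean | f | ITT difference | Power, 29 per arm | Power, 30 per arm |
|---|---|---|---|---|
| DCC mean (k = 0) | 10% | 4.69 | 70.8% | 72.4% |
| DCC mean (k = 0) | 20% | 4.17 | 60.2% | 61.7% |
| 2.6 below DCC | 10% | 4.43 | 64.6% | 66.1% |
| 2.6 below DCC | 20% | 3.65 | 47.2% | 48.6% |
| 2.6 above DCC | 10% | 4.95 | 76.2% | 77.7% |
| 2.6 above DCC | 20% | 4.69 | 71.8% | 73.3% |

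A simulation of 40,000 trials for k = 0 at 29 per arm gave 70.7% and 59.8%.

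**Step 3: effect in treated infants needed for 80% ITT power (k = 0).** Solving step 2 for d:

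- 29 per arm: 5.84 points (5.84/52.1 = 11.2% relative) at f = 10%; 6.67 points (12.8%) at f = 20%.
- 30 per arm: 5.73 points (11.0%) at f = 10%; 6.55 points (12.6%) at f = 20%.

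**Step 4: covariate gain needed to offset the loss (k = 0).** Multiplying both SDs by √(1 − R²), 80% power needs R² of about 0.20 (10%) to 0.37 (20%) at 29 per arm, and about 0.17 to 0.35 at 30.

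**The case against.** **It is not a calculation error.** This stands. The sample size follows exactly from its inputs; the question is which effect the 10% describes.

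**The 5.21 points may already be an assignment-level target.** Section 14.7 takes only the DCC value from the cited trial, the 10% rise is the investigators' own hypothesis, and 14.2 adopts a treatment-policy strategy. This reading is possible, but 14.7 attributes the rise to EPT and never says that it allows for failures. The loss of power is therefore conditional on the other reading, and 14.7 should say which one applies.

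**The haematocrit of non-feasible infants is unknown.** This stands. Section 10.2.1.6 allows immediate clamping, which could put them below the DCC mean, or cord milking, which section 6 credits alongside DCC with a higher blood volume. A reader might infer that they must do worse than controls; the documents do not support that. Even 2.6 points above the DCC mean, however, power stays below 80%.

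**The 10–20% may not carry over.** It refers to elective caesareans. The exclusion of placenta accreta or increta, and of abruption or previa with haemorrhage, could lower it; failures during resuscitation could raise it. Measuring it is itself a study aim.

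**ANCOVA may recover the loss.** It may, since sizing used an unadjusted test. But no R² is stated, and 14.7 already assigns the gain to missing values. Early clamping among controls (10.2.1.3) could also widen the contrast, again with no rate given.

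**Safeguards exist.** Feasibility and reasons for deviation are recorded (14.4.3), and a per-protocol analysis is planned. Both help interpretation; neither changes the power of the primary analysis.

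**Conclusion.** The point holds in conditional form. Section 14.7 gives 80% power without qualification and without allowing for a dilution that the protocol itself expects. If 5.21 points is the effect in infants who receive EPT, and non-feasible infants average the DCC mean, unadjusted ITT power is about 72% to 62% at the planned 30 per arm for 10% to 20% non-feasibility, and 71% to 60% at 29. At 29 per arm the illustrative range runs from 47% (20% non-feasible, 2.6 points below the DCC mean) to 76% (10% non-feasible, 2.6 points above).

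A reader might go further and state that the trial's power is 60–71%. The documents do not support that as a fact: they give neither the non-feasibility rate in this population nor the haematocrit of such infants, and they do not quantify the ANCOVA gain. Nor do they show that non-feasibility alone would explain a null result.

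**What to change.** Keep 60 births, the ITT primary analysis and the planned per-protocol analysis. Restate the power in 14.7 with its assumption, for example:

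> *For a 5.21-point effect in infants receiving EPT, and 10–20% non-feasible infants at the DCC mean, unadjusted ITT power is about 62–72% at 30 per arm (60–71% at 29). Power of 80% requires an effect in treated infants of about 5.7–6.5 points (5.8–6.7 at 29).*

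Add that any gain from ANCOVA is unquantified and already assigned to missing values. If the investigators mean 5.21 points as the ITT difference with non-feasibility already included, 14.7 should say so, together with the effect in treated infants that this implies.

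Replacing the per-protocol analysis with a complier-average estimate (the ITT difference divided by the difference in EPT receipt) is not advised. That estimate requires assignment to make no difference in non-feasible infants. Under 10.2.1.6 they may receive immediate clamping or milking where a control would receive DCC. With k = −2.6 the ratio would be 4.429/0.9 = 4.92 or 3.648/0.8 = 4.56, not 5.21.

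The cost is one rewritten paragraph with a less favourable power figure. No extra infants and no change of procedure are needed. For comparison, restoring 80% through sample size under the DCC-mean assumption would take about 36 per arm (10%) to 46 per arm (20%).

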| STUDY DESIGN       | Randomized, single-center, two-arm parallel, rater-blinded intervention study.                                                                                                                                                                                                                                                                                                                                                                                                                                                                                                                                                                                                                                                                |
| STUDY ARMS         | 
 
1) Intervention group: Extrauterine placental transfusion (EPT)
 
2) Control group: Delayed cord clamping (DCC)
 
                                                                                                                                                                                                                                                                                                                                                                                                                                                                                                                                                        |
| SAMPLE SIZE        | 60 births (including up to 30% twin pregnancies) in two arms of 30 birth                                                                                                                                                                                                                                                                                                                                                                                                                                                                                                                                                                                                                                                                      |

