## **9.7 APPROACH TO DICHORIAL TWIN PREGNANCY**

For obstetric reasons, birth of both twin infants each with their own placenta is not applicable in a majority of dichorial twin birth.

However, if the inclusion criteria of the study are basically fulfilled in case of twin pregnancy, dichorial twins can also be included in the study.

In this case, a delayed cord clamping (DCC) procedure is always performed for twin 1 (defined as the baby that the obstetrician develops first after caesarean section).

Twin 2 is randomized to receive either EPT or DCC depending on the randomization assignment. The firstborn twin will be recorded with respect to the primary outcome measure and, as far as possible, with respect to the secondary outcome measures.

The second-born randomized twin will be assigned to the neonatal resuscitation unit, which will allow measurement of all target criteria, including respiratory function monitor.

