## **14 STATISTIC**

### **14.1 STATISTICAL AND ANALYTICAL PLAN**

Quantitative target values are described with the number of valid and missing values, mean, standard deviation and percentiles (0, 25, 50, 75, 100 (%)), qualitative target values with absolute (n) and relative (%) frequency. In broad aspects, the statistical analysis is based on a descriptive analysis. P-values are to be interpreted two-sided (exceptions are marked), accordingly two-sided confidence intervals (to the 95% level) are given.

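### The paired twin test in section 14.7 compares second-born EPT infants with first-born DCC siblings, so it cannot separate the EPT effect from birth order

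*Protocol*

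**What the plan says.** Section 9.7 sets the rule for dichorionic twins: "In this case, a delayed cord clamping (DCC) procedure is always performed for twin 1". Twin 1 is defined there as the infant delivered first at the caesarean. Twin 2 receives EPT or DCC according to the envelope. Sections 9.3, 10.2.1.2 and 10.2.1.5 agree that only the second-born is randomised. Section 10.2.1.5 adds that the two infants are cared for on different resuscitation units and that twin 1's unit lacks the extended respiratory monitoring. Section 9.7 also has the primary outcome recorded for the first-born, with no restriction by arm.

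After the main sample size, section 14.7 states that "the nine twins randomized to EPT will be compared to their control siblings, where the paired t-test still achieves a power of 80"%. The level is a one-sided 10%, and the calculation assumes "a correlation of 0.5 between the two measurements (power pairedmeans"). Section 14.7 mentions neither birth order nor the twin pairs allocated to DCC.

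The number nine is 30% of the 30 births in one arm. The synopsis gives the twin share as a ceiling ("60 births (including up to 30% twin pregnancies) in two arms of 30 birth"), while section 9.3 gives about 30%.

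**The concern.** A paired test is attractive because siblings share a mother, a pregnancy and a gestational age. It estimates a treatment effect only if treatment is assigned at random within the pair, or if the two positions in the pair would otherwise give the same outcome. Here the position is fixed. The first infant out always gets DCC, and the EPT infant is always the second.

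Any systematic difference in early hematocrit between second-born and first-born twins therefore enters the paired estimate in full. So does any effect of the different resuscitation place. A birth-order difference in favour of the second twin could look like an EPT benefit, and one in the other direction could hide a real benefit. The test concerns the primary outcome variable, sits beside the main calculation with the same 80% figure, and is not labelled exploratory.

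**Working it through.** **Inputs, all from section 14.7.** DCC mean 52.1, SD 6.6; EPT mean 57.31, SD 7.26; difference 57.31 − 52.1 = 5.21 points; correlation 0.5; nine pairs; one-sided 10%.

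**Step 1: the plan's own figure.**
- SD of the within-pair difference: √(6.6² + 7.26² − 2 × 0.5 × 6.6 × 7.26) = 6.95.
- Noncentrality: 5.21 × √9 / 6.95 = 2.25, with 8 degrees of freedom.
- Power from the noncentral t distribution at one-sided 10%: **0.801**.

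The stated 80% reproduces. It depends on its inputs: eight pairs give 76.0%, and nine pairs with correlation 0.3 give 69.8%. Nine pairs at two-sided 5% with correlation 0.5 give 50.7%.

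**Step 2: what the paired difference estimates.** Let τ be the EPT effect and β the second-minus-first difference that would exist without EPT, including any effect of the resuscitation place.

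| Pairs | Twin 1 | Twin 2 | Expected twin 2 minus twin 1 |
|---|---|---|---|
| Allocated to EPT | DCC | EPT | τ + β |
| Allocated to DCC | DCC | DCC | β |

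The test in section 14.7 uses only the first row and so tests τ + β = 0. Subtracting the second row from the first gives τ, and that contrast is randomised. Allocation is 1:1 and stratified by singleton or multiple (section 9.4), so about as many pairs should fall in each row.

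**Step 3: how much β could matter.** The documents give no value for β, so the values here are assumptions and both signs are shown. With no EPT effect, both SDs are 6.6, and at correlation 0.5 the SD of the difference is √(6.6² + 6.6² − 6.6²) = 6.6. The noncentrality is β × 3 / 6.6 with 8 degrees of freedom.

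| Assumed β (points) | Rejection rate, nominal 10% |
|---|---|
| +3 | 50% |
| +2 | 34% |
| +1 | 20% |
| 0 | 10% |
| −1 | 4% |
| −2 | 2% |

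With a true EPT effect of 5.21 and β = −2, the noncentrality is 3.21 × 3 / 6.95 = 1.39 and the power falls from 80% to 51%.

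**Step 4: power of the randomised alternatives, 9 vs 9 pairs, correlation 0.5.**
- *Difference of differences.* The SDs are 6.95 (EPT pairs) and 6.60 (DCC pairs). Standard error: √(6.95²/9 + 6.60²/9) = 3.20. Noncentrality: 5.21 / 3.20 = 1.63, with about 16 degrees of freedom. Power: **62%** at one-sided 10%, **33%** at two-sided 5%.
- *ANCOVA of twin 2 on arm and twin 1.* Pooled SD: √((6.6² + 7.26²)/2) = 6.94. Residual SD: 6.94 × √(1 − 0.5²) = 6.01. Standard error: 6.01 × √(2/9) = 2.83. Noncentrality: 5.21 / 2.83 = 1.84, with 15 degrees of freedom. Power: 69% and 41%. Allowing for chance imbalance in the covariate, with the standard error raised by √(1 + 1/14), gives 67% and 38%. The range is therefore **67–69%** and **38–41%**.

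**The case against.** The strongest reply is that this is a supplementary test with fully disclosed settings and nothing depends on it. Section 14.1 calls the analysis largely descriptive. Section 14.7 attaches no decision rule to the paired test. The primary comparison is the ANCOVA in the randomised population (sections 14.2 and 14.3), and among twins the randomised infant is the second-born in both arms, so birth order does not bias it. Section 14.6 also plans a subgroup analysis of singletons against multiples, which would compare second-born infants across arms. All of this stands, and it limits how serious the point is. It does not repair the paired test: the subgroup analysis is a different analysis, and the test as stated still takes birth order for treatment.

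A reader might infer several stronger claims that the documents do not support:
- *That the one-sided 10% level contradicts section 14.1.* That section says "P-values are to be interpreted two-sided (exceptions are marked"), and section 14.7 marks this one openly. The level is lenient but declared.
- *That the 80% is miscalculated.* It reproduces at 0.801.
- *That nine pairs is the maximum.* The synopsis wording suggests a ceiling, but section 9.3 makes nine an expected number. The two statements need reconciling.
- *That a positive result would be presented as confirming the primary finding.* The protocol does not say so.
- *That birth order is known to inflate the result.* No size or direction is given, so the rejection rates above only illustrate how sensitive the test is.

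**Conclusion.** The point holds as a should-fix. In the pairs that section 14.7 uses, treatment and birth order coincide completely, so the paired t-test cannot isolate the EPT effect. This follows from the protocol's own allocation rule and needs no assumed figure. Only the size of the possible distortion is unknown.

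The cost of a valid comparison can be calculated under the protocol's effect, SDs and correlation of 0.5, with nine pairs per arm. At one-sided 10%, power falls from 80% to 62% for the difference of differences, or to 67–69% for the ANCOVA. At two-sided 5% it is 33% or 38–41%. These figures would change with another correlation, for which the protocol cites no source, or with fewer pairs. The main sample size and the primary analysis are not touched.

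**What to change.** Replace the paired t-test sentence in section 14.7 with one randomised contrast, chosen in advance:
- the twin 2 minus twin 1 hematocrit difference, compared between EPT-allocated and DCC-allocated pairs; or
- ANCOVA of twin 2's hematocrit on arm, with twin 1's hematocrit as covariate. This has the higher power at the assumed correlation.

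Label it exploratory, report the estimate with a two-sided 95% CI, and restate the power for the method chosen, using the figures in step 4. The two methods have different power, so one figure cannot serve for both. If the within-pair difference in EPT pairs is still wanted, show it descriptively beside the same difference in DCC pairs. Reconcile the twin share in the synopsis with that in section 9.3, and say whether nine pairs per arm is a limit or an expectation.

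The change is wording only. Twin 1's primary outcome is already to be recorded, and randomisation already supplies the DCC pairs. The price is a lower stated power for a supplementary analysis.
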